**1.9.1 Definitions of which AE and SAE that are to be reported in the CRF**

In this study, all cases of BON, renal insufficiency, hypo-, and hypercalcaemia will be reported as an Adverse Event (AE) or a Serious Adverse Event (SAE). An adverse event is any new, undesirable medical occurrence or change of an existing condition, whether or not it is considered related to the treatment. A serious adverse event includes, but may not be limited to:

-Death due to study medication

-Life threatening complications

-Inpatient hospitalisation or prolongation of existing hospitalisation

-Significant and persistent disability / incapacity

-An event that may require medical or surgical intervention to prevent one of the outcomes list above

In this study, temporary renal insufficiency that can be reversed either by fluid replacement or by treatment reduction will be perceived as an AE, persistent renal insufficiency will be perceived as a SAE. Persistent grade 2 BON or any grade 3 BON will be perceived as a SAE

Renal insufficiencies, hypo-, and hypercalcaemia:

Renal insufficiency hypo-, and hypercalcaemia AEs will be graded according to the National Cancer Institute Common Toxicity Criteria for Adverse Evens (NCI CTCEA) version 4.0. All AEs should be reported and related to the study drug administration as follows:

Not related:

An adverse event, which is not related to the use of the drug.

Unlikely/doubtful:

An adverse event for which an alternative explanation is more likely, e.g., concomitant drug(s),

concomitant disease(s), or the relationship in time suggests that a causal relationship is unlikely.

Possible:

An adverse event, which might be due to the use of the drug. An alternative explanation, e.g., concomitant drug(s), concomitant disease(s), is inconclusive. The relationship in time is reasonable,therefore, the causal relationship cannot be excluded.

Probable:

An adverse event, which might be due to the use of the drug. The relationship in time is suggestive (e.g., confirmed by repetition). An alternative explanation is less likely, e.g., concomitant drug(s), concomitant disease(s).

Definitive/very likely:

An adverse event that is listed as a possible adverse reaction and cannot be reasonably explained by

an alternative explanation, e.g., concomitant drug(s), concomitant disease(s). The relationship in

time is very suggestive (e.g., it is confirmed by de-challenge and re-challenge).

BON:

BON is a rare occurring event and should always be reported as at least possible related. If the patient has received radiation therapy to the neck or mandibular region one should keep the differential diagnosis of osteoradionecrosis in mind. If the treating clinician discovers cases of osteoradionecrosis this should still be reported as a possible case of BON.

Bon will be graded according to the 2009 AAOMS position paper on BON [[30](#_ENREF_30)].

Stage 0: No clinical evidence of necrotic bone, but nonspecific clinical findings and symptoms.

Stage 1: Exposed and necrotic bone in asymptomatic patients without evidence of infections.

Stage 2: Exposed and necrotic bone associated with infections as evidenced by pain and erythema in region of exposed bone with or without purulent drainage.

Stage 3: Exposed and necrotic bone in patients with pain, infection, and one or more of the following: exposed and necrotic bone extending beyond the region of alveolar bone, (ie, inferior border and ramus in the mandible, maxillary sinus and zygoma in the maxilla) resulting in pathologic fracture, extraoral fistula, oral antral/oral nasal communication, or osteolysis extending to the inferior border of the mandible or the sinus floor.

Exceptions to AE and SAE reporting.

Hospitalisations or prolongation of hospitalisation due to progression of MM or well-known complications to multiple myeloma e.g. infection or anaemia do not need to be reported to the study secretariat, nor must a SAE report be completed. It also applies to complications to administration of myeloma treatment, other elective measures or for social reasons. Death due to progression of multiple myeloma do not need to be reported as an SAE.

All SAR (1.9) and all selected SAE (1.9.1) must be reported to the study secretary within one month of discovery or notification of the event. The following data must be assigned: description, dates of onset and resolution, severity, assessment of relatedness to study treatment, other suspected drugs or devices, and action taken. The investigator may be asked to provide follow-up information. It will be left to the investigator’s clinical judgement whether or not an adverse event is of sufficient severity to require that the patient should be removed from treatment. A patient may also voluntarily withdraw from treatment due to what he or she perceives as an intolerable adverse event. If either of these occurs, the patient should undergo an end of study assessment, in which reason for end of study should be noted and be given appropriate care under medical supervision until symptoms cease or the condition becomes stable.

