**1.9 Side Effects.**

Zoledronic acid has been approved by EMEA since 2001 for prevention of SRE in adult patients with advanced malignancies involving the bone. It has been used extensively for many years and has a well-known toxicity profile. It is not financially possible to conduct a new study where all possible side effects will be reported rigorous, as no pharmaceutical companies have shown interest in the study. Furthermore, it is unlikely that new – still unknown – side effects can be identified from this study since all patients most likely will receive multiple lines of anti-myeloma chemotherapeutics that will differ from site to site, and a significant portion of the patients will die due to progressive disease during the protocol. However, the Nordic Myeloma Study Group finds it very relevant to conduct a study with focus on BON, which is a late occurring, severely disabling side effect where the incidence increases proportionally to the exposure time. In this study, we will focus on BON and renal insufficiency as this is a common clinically relevant side effect to zoledronic acid. Patients will furthermore be evaluated using QoL, which ultimately will answer the question whether prolonged treatment with zoledronic acid is of benefit for these severely ill patients. All AEs and SAEs will be documented in the patient’s medical journal but will not be reported in the CRF if they can be related to the myeloma disease or to the chemotherapeutic treatment the patient receives. All SAR and SUSAR will be reported in the CRF. The treating physician decides if an AE or SAE is related to the investigational compound and thus should be reported as an SAR / SUSAR. Summary of Product Characteristics supplied in appendix 5 will be used as reference document to decide if a SAR should be upgraded to a SUSAR. All cases of renal insufficiency, BON, hypo-, and hypercalcaemia, will be reported in the CRF regardless of causality.

Registration of predefined (section 1.9.1 and 1.9.2) AEs, SAEs, SAR, and SUSARs will continue until the last infusions at year 4 +30 days for the treatment group or until year 4 +30 days for the observation group.

All national SAE, SAR, and SUSARs reported in the CRF during the trial will be listed and reported yearly by the national investigator to the National Health Authority and to the National Ethics Committee according to the national regulations by the national study secretary.

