**1.10 Concomitant Therapy.**

All concomitant therapy are permitted, however caution is advised when zoledronic acid is given together with aminoglycosides, non-steroid anti-inflammatory drugs (NSAID), or other potential nephrotoxic drugs, as both MM in itself and zoledronic acid are potentially nephrotoxic.

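### Two conflicts in the safety reporting rules of 1.9.1 leave it open whether a renal or hypercalcaemia admission counts as an SAE, and the yearly stopping review uses SAE numbers by arm

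*Protocol*

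**What the plan says.** Protocol section 1.9 starts from a general exclusion: AEs and SAEs stay in the medical journal and "will not be reported in the CRF if they can be related to the myeloma disease or to the chemotherapeutic treatment the patient receives". It then makes an exception for four event types: "All cases of renal insufficiency, BON, hypo-, and hypercalcaemia, will be reported in the CRF regardless of causality".

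Section 1.9.1 repeats that all cases of these four are reported, as an AE or an SAE. It lists what makes an event serious, including "Inpatient hospitalisation or prolongation of existing hospitalisation". For the kidney it adds that "temporary renal insufficiency that can be reversed either by fluid replacement or by treatment reduction will be perceived as an AE", while persistent insufficiency is an SAE.

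The AE and SAE definitions in 1.9.1 end with exceptions. Hospitalisations "due to progression of MM or well-known complications to multiple myeloma e.g. infection or anaemia do not need to be reported" to the study secretariat, and no SAE report has to be completed. The waiver is then widened: "It also applies to complications to administration of myeloma treatment, other elective measures or for social reasons". The four mandatory events are not mentioned there.

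Three other places bear on this:

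- Section 1.3 names hypercalcaemia among the results of myeloma bone destruction, and 1.10 says that "both MM in itself and zoledronic acid are potentially nephrotoxic".
- Under 1.9 the treating physician judges whether an event is related to the study drug, and 1.15 says the study is not blinded.
- Under 1.9 the steering committee reviews the numbers of SAEs, SARs and SUSARs in the two arms each year, and decides on that basis whether to end the study early.

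**The concern.** A site that admits a patient with renal failure or hypercalcaemia finds two instructions in the same section. One says that every such case is reported, whatever the cause. The other says that an admission for a known complication of myeloma needs no SAE report. Nothing says which prevails.

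The renal rule adds a second, independent difficulty. Admission makes an event serious, yet a renal event that reverses with fluids or treatment reduction is an AE. The renal sentence does not say what happens when the reversible case was admitted.

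At stake is the SAE count by arm. Section 1.9 names renal insufficiency as one of the two toxicities on which the trial focuses. If the form can be omitted when the physician puts the event down to myeloma, and the physician knows whether the patient is on zoledronic acid, the count can differ between arms for reasons other than true frequency. That count goes to the committee that may stop the trial.

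**Working it through.** No arithmetic applies. The protocol states no renal or calcium event rate, admission rate or attribution rate, so the check sets the rules side by side for each kind of case.

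| Case | Report-all rule, seriousness list and renal sentence | Exceptions in 1.9.1 | Result |
| --- | --- | --- | --- |
| Renal, reversible, not admitted, no other seriousness criterion met | AE | Not reached (concern admissions) | Consistent |
| Renal, persistent, not admitted | SAE | Not reached | Consistent |
| Renal, persistent, admitted, not put down to myeloma or its treatment | SAE | Not reached | Consistent |
| Renal, persistent, admitted, put down to myeloma or its treatment | SAE | SAE report waived | Conflict 1 |
| Renal, reversible, admitted, not put down to myeloma or its treatment | SAE by admission, AE by the renal sentence | Not reached | Conflict 2 |
| Renal, reversible, admitted, put down to myeloma or its treatment | SAE by admission, AE by the renal sentence | SAE report waived | Conflicts 1 and 2 |
| Hypercalcaemia, admitted, put down to myeloma | SAE by admission | SAE report waived | Conflict 1 |

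**Does the exception reach these events?** Its examples are infection and anaemia, but they are given only as examples. Sections 1.3 and 1.10 supply the link for hypercalcaemia and for the kidney. BON is in practice outside it, because 1.9.1 requires BON always to be reported as at least possibly related. The protocol does not describe hypocalcaemia as a myeloma complication; 1.8 lists it as a side effect of the drug. The live cases are therefore renal insufficiency and hypercalcaemia.

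**Where does cause decide the count?** Compare the two rows for persistent, admitted renal insufficiency. They differ only in the physician's judgement of cause, and only one clearly yields an SAE form. Conflict 2 is different: it turns on reversibility, applies in the same way to both arms, and arises whatever the cause. It makes the count uncertain but cannot by itself create attribution bias.

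**What is outside the problem?** The waiver concerns the report to the secretariat and the SAE form. It does not withdraw the rule in 1.9 that all four event types enter the CRF. Section 1.8 has creatinine and ionised calcium measured monthly and recorded in the CRF, and 1.9.1 grades renal and calcium events by CTCAE version 4.0.

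**Where does the exposed number go?** To the yearly review in 1.9, which is framed in counts of SAEs, SARs and SUSARs rather than laboratory values or all-cause AEs. No numerical threshold is set.

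**The case against.** The strongest reply is that the specific rule governs. Section 1.9 states the attribution-based exclusion first and then lifts it for exactly these four events. The exceptions in 1.9.1 are general, and neither of their examples is one of the four. The paragraph directly after them still asks for all selected SAEs under 1.9.1 to be reported. The exception also only removes a duty; it does not forbid a report. The renal sentence can be read as a deliberate trial-specific classification.

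Part of this stands. A careful site could resolve the first conflict in favour of reporting, and no site is told not to report. But a paragraph labelled as exceptions is naturally read as limiting the rules before it. The paragraph after it does not help, because 1.9.1 contains both the rule and the exception. An optional report still leaves the count to the site.

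A reader might go further and infer that the whole renal safety comparison depends on open-label attribution. The protocol does not support that. All cases go into the CRF whatever the cause, with CTCAE grades and monthly creatinine and calcium, so an attribution-free comparison is available. Renal events are also not a listed endpoint in 1.5.

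A reader might also infer a known direction of bias against the continued-treatment arm. For renal events that is plausible but not shown. For hypercalcaemia the protocol gives no reason to expect it, since 1.8 does not name it among the main side effects of the drug. Myeloma hypercalcaemia above the stated limit in two consecutive samples is also captured through the PBD definition in 1.5.

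**Conclusion.** The point holds for the SAE count and its reporting to the secretariat, and no further. Section 1.9.1 contains two unresolved conflicts: the report-all rule against the hospitalisation exception, for renal insufficiency and hypercalcaemia; and the hospitalisation criterion against the reversible-means-AE rule, for renal insufficiency. The first lets an unblinded judgement of cause decide whether an admission is counted. The second leaves the class of an admitted, reversible renal case undefined in both arms.

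The size cannot be stated from the protocol. The conclusion assumes that some sites will read the open-ended exception as covering these events, which the wording permits but does not compel. It also assumes that the yearly review works from the counts that 1.9 names. The all-cause CRF and laboratory data remain sound. This should be corrected because it bears on a termination decision and is cheap to put right; it does not undermine the trial's efficacy analysis.

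**What to change.** 1. Add to the exceptions in 1.9.1: *These exceptions do not apply to BON, renal insufficiency, hypocalcaemia or hypercalcaemia, which are reported in both arms whatever the cause.*
2. Reconcile the renal AE/SAE sentence with the seriousness list, so that a renal event leading to admission is classed by the listed criteria, whether or not it later reverses.
3. In the description of the yearly review in 1.9, add that the steering committee also receives all-cause renal and calcium events by arm, taken from the CRF.

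The third step uses data already collected and would protect the review even if some sites applied the exception differently in the past. The cost is a few more SAE forms for renal and hypercalcaemia admissions put down to myeloma. No visit, test or treatment rule changes.

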**1.9.2 Definitions of which SUSAR that are to be reported**

All Suspected Unexpected Serious Adverse Reaction (SUSAR) possibly related to the study drug shall be reported to the sponsor. A SUSAR is a suspected unexpected Adverse Reaction which occur in the trial and that are both unexpected and serious. Suspected expected adverse reactions (SAR) are those AEs of which a reasonable causal relationship are known and described in medicinal product, of the compounds the patients is currently receiving, are not to be reported.

All SUSARs must be reported to the national study secretary within 24 hours of discovery or notification of the event. The following data must be assigned: description, dates of onset and resolution, severity, assessment of relatedness to study treatment, other suspected drugs or devices, and action taken. The investigator may be asked to provide follow-up information.

A SUSAR resulting in death or judged as life threatening must be reported to the sponsor, the other national investigators, the regulatory authorities and the ethical committee within 7 days after the national investigator has been notified about the event. A full report has to be sent to the national authorities within 15 days by the national study secretary.

A SUSAR, which is not resulting in death or is life threatening, has to be reported to the sponsor, the other national investigators, the regulatory authorities and the ethical committee within 15 days after the national investigator has been notified about the event. A full report has to be sent by the national study secretary to the national authorities as soon as possible.

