**1.2 Abbreviations.**

AE Adverse Event

bALP Bone specific Alkaline Phosphatase

BON Bisphosphonate Induced Osteonecrosis of the Jaw

Clcr Creatinine Clearance

CRF Case Report Form

CT Computed tomography

CTX-I C-terminal cross-linked Telopeptide of type I Collagen

ICTP C-terminal cross-linked Telopeptide of type I Collagen generated by MMPs

MGUS Monoclonal Gammopathy of Undetermined Significance

MM Multiple Myeloma

PINP Procollagen type I N-terminal propeptide

PBD Progressive Bone Disease

sPBD Symptomatic Progressive Bone Disease

SAE Severe Adverse Event

SAR Serious Adverse Reaction (expected)

SRE Skeletal Related Event

SUSAR Suspected Unexpected Serious Adverse Reactions

TRAP5b Tartrate Resistant Acid Phosphatase isotype 5b

QoL Quality of Life

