All SUSARs will be listed and reported yearly by the sponsor to the national investigators and to the Danish Health Authorities.

Annually the steering committee will discuss the numbers of SAE, SAR, and SUSARs in the two patient arms. Based on these data the committee will decide if the study should be terminated before time. Likewise an interim analysis will be conducted when half the patients have completed the study. If significant relevant different is observed already at this time-point the study will also be terminated for the benefit of the remaining patients

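### Section 1.9.2 tells sites not to report the expected reactions (SAR) that 1.9 and 1.9.1 require, and defines SAR differently, so the yearly SAR counts by arm may be incomplete

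*Protocol*

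**What the plan says.** Section 1.2 (Abbreviations) makes the category both serious and expected: "SAR Serious Adverse Reaction (expected)". Section 1.9 (Side Effects) then states: "All SAR and SUSAR will be reported in the CRF". It names the product summary in appendix 5 as the reference for deciding whether a SAR becomes a SUSAR. Section 1.9.1 adds a deadline and a recipient: "All SAR (1.9) and all selected SAE (1.9.1) must be reported to the study secretary within one month of discovery".

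Section 1.9.2, on SUSARs, says something else. It begins: "Suspected expected adverse reactions (SAR) are those AEs of which a reasonable causal relationship are known and described in medicinal product". It ends by saying that such reactions "of the compounds the patients is currently receiving, are not to be reported".

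The counts have a stated use. Section 1.9 says: "Annually the steering committee will discuss the numbers of SAE, SAR, and SUSARs in the two patient arms". It continues: "Based on these data the committee will decide if the study should be terminated before time". It also has the SARs held in the CRF listed each year for the national authorities and ethics committees.

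**The concern.** Two sections order that SARs be reported and a third says, without qualification, that they are not. A site could comply with either instruction and point to the protocol. If sites choose differently, the number of SARs in each arm depends on which section a site followed as well as on what happened to its patients. Those numbers go before a committee that may stop the trial on them, and into the yearly listings for the authorities.

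The differing definitions add a second problem. Even sites that agree to report SARs may not agree on which events are SARs.

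**Working it through.** No sample size, power or event figure is involved, so the check is a comparison of the texts.

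1. **Is it the same category?** All the sections use the label SAR. Section 1.2 requires the reaction to be serious and expected. Section 1.9.2 requires it to be expected and causally plausible, speaks of AEs, and does not mention seriousness. On its face the 1.9.2 category is the wider one, so the serious expected reactions of section 1.2 fall inside it and its exclusion reaches them.

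2. **Expected in relation to what?** Section 1.9 judges expectedness against the zoledronic acid product summary in appendix 5, and has the treating physician decide whether an event is related to the investigational compound. Section 1.9.2 refers to all the compounds the patient is receiving. Section 1.6 allows any concurrent anti-myeloma treatment, so the two yardsticks can differ in practice. Take a serious event suspected to be due to zoledronic acid, absent from appendix 5 but known for a concurrent drug. Under 1.9 it is a candidate SUSAR. Under the wording of 1.9.2 it can be read as an expected reaction that is not reported.

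3. **Do the rules conflict?** Section 1.9 requires CRF entry of all SARs. Section 1.9.1 requires a report to the study secretary within one month. Section 1.9.2 requires no report and attaches no route or time limit to that exclusion. The three cannot all be followed as written.

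4. **Would a site turn to 1.9.2 for this?** Section 1.9 sends it there: "Registration of predefined (section 1.9.1 and 1.9.2) AEs, SAEs, SAR, and SUSARs will continue until the last infusions at year 4 +30 days". Section 1.9.2 is thus one of the two places said to define what is registered.

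5. **Which events are exposed?** Section 1.9 has renal insufficiency, osteonecrosis of the jaw, and low and high calcium entered in the CRF whatever their cause, and section 1.9.1 makes them the selected AEs and SAEs. Those counts do not depend on 1.9.2. What is exposed is every other expected serious reaction.

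6. **In which direction?** Under section 1.7, patients recruited at diagnosis all receive zoledronic acid in years 0-2, before they have an arm. From year 2, arm A stops and arm B continues. Patients entering under the amendment go straight to randomisation. For years 2-4, unreported reactions to zoledronic acid would therefore be expected mainly in arm B, which would shrink the difference between arms that the committee sees. This is an inference from the design; the protocol does not state it.

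7. **How large?** The protocol gives no SAR rate and no basis for guessing how many sites would follow 1.9.2 literally. No figure can be derived.

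**The case against.** The best defence is context. Section 1.9.2 is headed as the definition of reportable SUSARs. Its first sentence concerns reporting to the sponsor, and the rest deals only with the 24-hour, 7-day and 15-day routes. Read there, the sentence most naturally means that expected reactions do not go by that route. SAR reporting is set out positively elsewhere: CRF entry, a one-month deadline with listed data items, registration to 30 days beyond year 4, and yearly listings. Section 1.12 also has SARs registered for 30 days after a patient leaves the study. A site would have to set all this aside for one awkward sentence. The plural reference to compounds may also be aimed at known reactions to background chemotherapy, which section 1.9 already keeps out of the CRF.

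Much of this stands. The narrower meaning is probably what was intended, and the two-tier scheme can be pieced together from 1.9 and 1.9.1. The sentence itself, however, contains no such limit, uses the same label as the sections it contradicts, and sits in a section that 1.9 cites as defining what is registered. If background therapy was the target, the text should not have called those reactions SARs.

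A reader might infer more: that all SARs outside the protected conditions are lost at such sites, or that the safety comparison as a whole is tilted towards longer treatment. The documents do not support either. The first only restates the assumption that a site reports nothing. The second overlooks years 0-2, when there are no arms to compare, and the protected events, which include the two the protocol says it will focus on (osteonecrosis of the jaw and renal insufficiency).

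**Conclusion.** The contradiction is in the current text and the point holds in limited form. Section 1.9.2 states a rule on SARs that conflicts with 1.9 and 1.9.1, and a definition that conflicts with 1.2 and 1.9. The yearly SAR counts by arm may be incomplete for expected serious reactions other than osteonecrosis of the jaw, renal insufficiency and calcium disorders. That conclusion assumes that at least some sites follow 1.9.2 literally, which the protocol neither shows nor rules out. The size is unknown. The direction, towards too few events in arm B, applies to years 2-4 only and is inferred. The primary endpoint, time to progressive bone disease, is not affected. The sentence should be corrected because the counts inform a termination decision, but it does not call the design into question.

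**What to change.** Reconcile sections 1.2, 1.9, 1.9.1 and 1.9.2 in two steps.

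- Use one definition of SAR throughout: a reaction that is serious, expected and related to the study drug, with expectedness judged against the reference document in appendix 5.
- In 1.9.2, replace the exclusion with a statement that SARs are exempt from the 24-hour, 7-day and 15-day SUSAR reporting, but are recorded in the CRF and reported to the study secretary within one month, as 1.9 and 1.9.1 already require.

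The cost is one replaced sentence and one aligned definition. No new data are collected, because the other two sections already ask for them.
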